**Table 1 T1:**
[figure not shown]
Summary of primary and secondary outcome variables assessed at baseline, 1, 3, and 6 months’ follow-up.

A pilot study and a preliminary study were undertaken to establish the appropriateness of assessment tools and the standardization of procedures.

Personal and sociodemographic variables are as follows:

Age (years);Sex (male or female);Weight (kg); Height (m); body mass index (BMI) (kg/m^2^);Study level (no studies, basic education, secondary school, or superior studies);Marital status (single, married, separated, divorced or widowed)Time since diagnosis of AD (years and months);Cognitive impairment [MMSE and The Global Deterioration Scale (GDS)]^[68,78]^;Smoking (yes or no);Falls in the last year (number);Pharmacological treatment (name and number of pills per day);Comorbidities (name).

#### Primary outcome variables

2.7.1

The primary outcome measures are the change in gait, balance, and bone health status during the study follow-up.

Physical functions such as gait and balance will be assessed by the POMA-T and the TUG. Both of them are widely and easily used tools applied in clinical settings with older adults and AD patients.^[16,30]^ And bone health status will be assessed by quantitative ultrasound (QUS).^[79–81]^

POMA-T: We will perform the original POMA-T 28-point version. It consists of a balance scale [Balance performance oriented mobility assessment (POMA-B)] and a gait scale [Gait performance oriented mobility assessment (POMA-G)]. POMA-B can score 16 points (sitting balance, get up and sit up from a chair, immediate standing balance in the first 3 to 5 seconds, standing balance, balance with eyes closed and turning balance 360°). POMA-G can score 12 points (initiation of gait, step height, step length, step symmetry, step continuity, path deviation, trunk stability, and walk stance). Less than 19 points means high risk of falls, between 19 and 24 means risk of falls, and between 24 and 28 means no disturbance in gait or balance. Therefore, the POMA-T's cutoff point that predicts moderate or high risk of falling and disturbance in balance and gait was 24.^[16,17,22,82,83]^TUG: Is an easy tool to evaluate the gait and balance. It measures the time in seconds for the subjects to get up from a standard armchair, walk 3 m, turn, walk back to the chair and sit down. The cut-off point for normal mobility is 12 seconds and values > 30 seconds indicate a high level of dependence,^[30,84,85]^ although other authors are somewhat stricter with the interpretation of the TUG, in such a way that with a time <10 seconds, it is considered normal; <20 seconds mobility difficulties and low or moderate risk of falls; > 20 mobility problems with need of help and high risk of falls.^[84]^Calcaneal QUS: The bone health status will be assessed by ultrasound bone densitometry/sonometry. It is a safe, radiation-free modality that provides precise quantitative assessment of skeletal status, useful information in elderly for identifying patients at risk of developing osteoporosis and for assessing their risk of future fracture.^[79,80,86]^ Bone mass we will measured at the calcaneus (95% of trabecular bone) by using QUS (Sahara Hologic Clinical Bone Sonometer; Hologic lnc., Waltham, MA). QUS parameters will be measured, but we consider the estimated BMD (g/cm^2^) and T-score (comparison of the average mineral density of the patient's bone with a healthy young people) as primary outcome, because some researchers suggested that these parameters are more useful in the determination of subjects with low bone health status.^[79–81,86]^

Quantitative ultrasound index (QUI) or stiffness index (SI) was calculated from BUA and SOS and expressed as absolute values. QUI is obtained by using the formula: QUI = (0.41x SOS) + (0.41x BUA)- 571.

Nutritional status: Mini Nutritional Assessment (MNA) to assess the nutritional status and the relationship with cognitive stage, bone status, and physical functions. The MNA consists of 18 questions, with the total MNA score ranging from 0 to 30, where higher score indicating a better nutritional status.^[90]^ The total score was used to classify each patient into well nourished (MNA score >23.5), at risk of malnutrition (MNA score = 17.0–23.5), or malnourished (MNA score <17). MNA has a high sensitivity, specificity, and reliability.

### Sample size calculation

2.8

The sample size calculation has been made based on the potential modification of the score of the POMA-T. For this, we have considered the results obtained in the previous pilot study with 9 patients in a 1-month follow-up, and the preliminary trial with 72 participants with a ratio of 3:1 to the intervention group and the control one during 6 months. In the pilot study, the POMA-T was modified by 1.7 points. Then, in the preliminary trial, we accepted to calculate the sample size, as statistically significant, with a difference greater than or equal to 1.7 points with a dropTout rate of 15%.

In our current study, the sample size has been estimated to conduct a randomized controlled clinical trial with a 1:1 ratio between the 2 groups. In this new calculation, considering the data from the pilot study and some of the available data from the preliminary trial, we have reduced the minimal detectable change in the POMA-T to 1.5 points, with a standard deviation of 2 points and we have increased the drop-out estimated rate during the study to 33% by the difficulty to avoid intervention biases in the control group fundamentally. Therefore, with this, and accepting an alpha risk of 0.05 and a beta risk of 0.2 in a 2-sided test, 84 subjects are necessary, 42 in each group. The sample size calculation was made with the software “GRANMO sample size and power calculator” (7.12 version).

### Statistical analysis

2.9

Data will be analyzed by using the IBM-SPSS software package (version 23.0). Descriptive data analysis will be reported by groups as means ± standard deviation for quantitative variables and as frequencies and percentages for qualitative variables. In the graphical representation, bar graphs by groups will be used for quantitative variables, and pie charts to represent categorical variables. The main change from baseline to 6 months will be calculated by using intention-to-treat analysis for each outcome measure.

Initially, for comparisons between groups at baseline, *t* tests or Mann–Whitney *U* tests will be used for continuous variables, depending on normality, which will be checked for each using the Kolmogorov–Smirnov test and normal probability box-plots, and the Chi-square test or Fisher test will be used for quantitative variables.

To analyze the efficacy of the multidomain intervention on the outcome variables, both in the primary and secondary outcomes, multivariate analysis of variance (MANOVA) will be applied with repeated measures (4 levels) to assess interactions between the factors and differences by categorical variables, with covariates, and pairwise comparisons post-hoc to determine whether there are significant differences between groups and within groups. The effect size for the MANOVA model will be calculated by the partial eta square (η^2^) that shows how much variance is explained by the independent variable.

We will carry out correlations with Pearson *r* coefficient to determine whether the values of 2 or more quantitative variables change in conjunction or are related in some of the moment of the study (time-factor in the statistical model).

For the analysis of the falls data, we will calculate the incidence rate during the study and the prevalence proportion by group and by sex at the end of the study (point prevalence). Subsequently, we will calculate the relative risk to estimate the magnitude of the association between the participation to the MPEP and falls, and indicate the likelihood of fall in the intervention group relative to the control group and also by sex.^[91]^

The statistical analysis will be conducted at a 95% confidence level. A *P* value < .05 will be considered to indicate statistical significance in all analyses.

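### The named efficacy analysis, a 4-level repeated-measures MANOVA, uses only patients with all four visits unless missing values are imputed, which conflicts with the promised intention-to-treat analysis at 33% drop-out; no single contrast is named as primary.

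*Protocol article*

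**What the plan says.** Section 2.9 (Statistical analysis) makes two statements about the same data. On the analysis principle: "The main change from baseline to 6 months will be calculated by using intention-to-treat analysis for each outcome measure". On the method, for primary and secondary outcomes alike: "multivariate analysis of variance (MANOVA) will be applied with repeated measures (4 levels", with unnamed covariates and post-hoc pairwise comparisons between and within groups. The four levels are baseline and the visits at 1, 3 and 6 months (section 2.7). The software is SPSS 23, and the effect size to be reported is partial eta squared. The article names no rule for missing visits and marks no contrast as primary.

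Section 2.8 (Sample size calculation) sizes the trial on a "minimal detectable change in the POMA-T to 1.5 points, with a standard deviation of 2 points", "accepting an alpha risk of 0.05 and a beta risk of 0.2 in a 2-sided test", and concludes that "84 subjects are necessary, 42 in each group". On losses it says "we have increased the drop-out estimated rate during the study to 33% by the difficulty to avoid intervention biases in the control group fundamentally".

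Section 2.5 lists among the exclusion criteria attendance at the exercise programme below 75% in any period between assessments, two or more consecutive weeks without sessions, and taking part in another programme, the last flagged as a bias for the control group. The two attendance criteria can arise only after allocation, and only in the arm that attends sessions. Section 3.1 repeats that exercise taken elsewhere is the difficulty with controls and may raise drop-out.

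**The concern.** Classical repeated-measures MANOVA works on a complete vector of responses. A patient who misses the 6-month visit, or only the 1-month visit, contributes nothing. When the protocol itself expects to lose a third of its patients, the named method yields a completer analysis, while the same section describes the result as intention-to-treat.

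Two things are at stake. The first is bias. Intervention patients can leave through poor attendance and controls through exercise elsewhere, so those who remain in the two arms may no longer be comparable. The second is which test decides the trial. The sample size rests on one difference between two means. The MANOVA interaction tests three changes at once, with baseline as one of the responses, and partial eta squared does not state a difference in points.

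**Working it through.** **1. The protocol's own figure.** Inputs from section 2.8: difference 1.5, SD 2, two-sided alpha 0.05, power 0.80, 1:1 allocation, drop-out 33%.

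n per arm = 2 × [2 × (1.960 + 0.842) / 1.5]² = 27.9, rounded up to 28. Inflated: 28 / (1 − 0.33) = 41.8, rounded up to 42. Total 84, which reproduces the stated figure exactly. So the test behind the sample size is a 1-df comparison of two means with 28 completers per arm. Its power is 0.80 by the normal formula and 0.79 by the t test.

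**2. Patients that a complete-vector analysis keeps.** 42 × 0.67 = 28.1 per arm, about 56 of 84. If a further 5% or 10% of the remaining patients missed each of the two earlier follow-up visits (an assumption), the count falls to 28.1 × 0.95² = 25.4 or 28.1 × 0.90² = 22.8 per arm. If all 42 per arm contributed, the two-mean comparison would have power 0.93 (normal) or 0.92 (t).

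**3. Bias among completers.** The documents give no drop-out model, so this one is assumed: no true effect, SD of change 2, correlation 0.7 between visits, 33% loss in each arm, and log-odds of leaving that depend on the change so far at 0.5 to 0.75 per 2 points. Simulation with 400,000 patients per arm gives these between-arm biases in the 6-month change:

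- the same dependence in both arms (0.5 each): about 0
- the same direction, slightly different strength (0.75 against 0.5): about 0.07
- dependence in one arm only: about 0.17 to 0.25
- opposite directions, strongest setting (0.75 each): just under 0.50

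Against the 1.5-point target, 0.2 is 13% and 0.5 is 33%. A smaller spread of change would give smaller values.

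**4. Power of the 3-df group-by-time test.** This is Hotelling's T² on the three changes from baseline, with non-centrality λ = (n/2) δ′Σ⁻¹δ and Σ = 4[(1 − r)I + rJ] (I the identity matrix, J the matrix of ones), referred to F with 3 and 2n − 4 = 52 df, n = 28. Example: δ = (0.25, 0.75, 1.5), r = 0.5. The sum of squares is 2.875 and the sum is 2.5, so δ′Σ⁻¹δ = (2.875 − 2.5²/4) / 2 = 0.656, λ = 14 × 0.656 = 9.19, and power is 0.685.

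| Assumed effect at 1, 3, 6 months | r = 0.3 | r = 0.5 | r = 0.7 |
|---|---|---|---|
| 0, 0, 1.5 | 0.682 | 0.802 | 0.951 |
| 0.25, 0.75, 1.5 | 0.648 | 0.685 | 0.819 |
| 0.5, 1.0, 1.5 | 0.678 | 0.661 | 0.735 |
| 1.5, 1.5, 1.5 | 0.889 | 0.802 | 0.718 |

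**5. The alternative.** A baseline-adjusted 6-month contrast has residual SD = 2 × √[(1 + ρ)/2], where ρ is the correlation of baseline with the 6-month score and 2 is the SD of change. That is 1.73, 1.84 and 1.90 for ρ = 0.5, 0.7 and 0.8. Power at 28 per arm is 0.89, 0.85 and 0.83, before counting any information from patients with partial follow-up.

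**The case against.** The strongest reply is that the article nowhere says patients are deleted. Imputed data could be fed to the MANOVA and all 84 analysed, and a rule for missing data is the kind of detail an article leaves to a fuller document. That stands as far as it goes: a reader might infer that the trial will certainly abandon intention-to-treat, and the text does not support that. The conflict is conditional on no imputation. It remains a point because the method is named here and is one that needs complete data.

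A reader might also infer that the omnibus test is underpowered. The table does not show this: power may fall below or above 0.80. The 33% is already built into the 84, so a completer comparison of two means keeps about 0.79 to 0.80.

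Nor does the article say that a 6-month comparison was the one powered. Section 2.8 gives 1.5 points without a visit, and the link to 6 months comes only from section 2.9. That section's post-hoc comparisons could yield a 6-month difference between arms, so the fair criticism is that none is designated as primary.

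The bias of about 0.5 needs poor responders to leave one arm and good responders the other. The documents describe exit routes that differ by arm, but not loss driven by response, so this figure is an upper illustration, not an expectation. Baseline as a repeated level and partial eta squared are conventional in this design; they cost efficiency and clarity but are not errors.

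**Conclusion.** The point holds in conditional form. Without imputation, the analysis named in section 2.9 uses about 28 of 42 patients per arm and is not the intention-to-treat analysis promised in the same section. Simple power is not the harm, since the sample size allows for the loss. The harm is exposure to bias, from about zero to about 0.5 points depending on an assumed drop-out mechanism, with about 0.2 if response drives loss in one arm only. Separately, the 3-df interaction is a different test from the one that gives 84, and its power (0.65 to 0.95 over the patterns tried, taking SD 2 as the SD of change) is not fixed by section 2.8. With no contrast named as primary, the result that decides the trial is open. The post-allocation criteria in section 2.5 sharpen the conflict, because patients meeting them would leave the data whatever model is fitted.

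**What to change.** Replace the MANOVA with a linear mixed model (SPSS MIXED) on all randomised patients with any follow-up. Use outcomes at 1, 3 and 6 months; fixed effects for arm, visit, arm × visit, baseline value and baseline × visit; and an unstructured covariance. Designate the 1-df difference between arms in POMA-T at 6 months as the primary result, in points with a 95% confidence interval. The model is valid if drop-out depends only on observed data, so add a sensitivity analysis for drop-out not at random, such as a delta-adjusted or reference-based one.

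Reconcile sections 2.5 and 2.9, so that patients who meet a criterion after allocation stay in the analysis set with the outcome data collected. Without this the mixed model does not restore intention-to-treat. This concerns who is analysed, not how anyone is treated.

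The cost is a little more analysis work in the same software, and continued assessment of such patients at visits already planned. No extra patients are needed.

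### For the continuous primary outcomes, the effect size named for the efficacy model is partial eta squared, which has no direction or units and cannot be set against the 1.5-point POMA-T difference that sizes the trial

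*Protocol article*

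**What the plan says.** Section 2.8 (Sample size calculation) defines the design effect in scale points: "we have reduced the minimal detectable change in the POMA-T to 1.5 points", "with a standard deviation of 2 points", and "accepting an alpha risk of 0.05 and a beta risk of 0.2 in a 2-sided test". With 1:1 allocation and drop-out raised to 33%, it concludes that "84 subjects are necessary, 42 in each group".

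Section 2.9 (Statistical analysis) sets out the efficacy model for primary and secondary outcomes: "multivariate analysis of variance (MANOVA) will be applied with repeated measures (4 levels"), with covariates and post-hoc pairwise comparisons. On effect size it states: "The effect size for the MANOVA model will be calculated by the partial eta square". It explains this figure as the share of variance due to the independent variable.

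The same section plans other summaries: means and SDs by group, the change from baseline to 6 months for each outcome by intention to treat, and a relative risk for falls. The pairwise comparisons are described as a search for significant differences between and within groups. The closing sentence on a 95% confidence level stands next to the P < .05 rule and does not attach an interval to any treatment difference. The section does not say whether the outcomes enter one MANOVA together or are modelled one at a time.

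**The concern.** The trial's size rests on a question in POMA-T points: is the difference between groups as large as 1.5? The effect size chosen for the model that judges efficacy cannot answer it.

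- **No sign.** Benefit and harm of equal size give the same value.
- **No units.** It cannot be converted to POMA-T points, TUG seconds or g/cm² without further information.
- **No single time point.** With measurements at baseline, 1, 3 and 6 months, a multivariate group-by-time value combines three contrasts and does not isolate the change to month 6.
- **Upward bias.** Its expected value is above zero when nothing has happened, and it grows with the number of dimensions in the model. Reading it simply as variance explained by the intervention is therefore unsafe in a trial of this size.

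At stake is interpretation. A report could give a P value and a partial eta squared for each primary outcome and still not say how large the treatment difference was or how precisely it was estimated.

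**Working it through.** **1. The plan's sample size (inputs from section 2.8).** Difference 1.5, SD 2, two-sided alpha 0.05, power 0.80, 1:1 allocation, drop-out 33%.

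- Per group: 2 × [2 × (1.960 + 0.842) / 1.5]² = 27.9, rounded up to 28.
- With drop-out: 28 / (1 − 0.33) = 41.8, rounded up to 42; total 84.

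This matches the stated figure. The expected number of completers on the plan's own terms is 2 × 28 = 56.

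**2. The design effect as partial eta squared (one outcome, one contrast).**

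- Standardised difference d = 1.5 / 2 = 0.75.
- Population value: d² / (d² + 4) = 0.5625 / 4.5625 = 0.123.
- Value when the observed difference is exactly 1.5 with 28 per group: F = [1.5 / (2 × √(2/28))]² = 7.875, and 7.875 / (7.875 + 54) = 0.127.
- With −1.5 in place of +1.5, F is again 7.875 and the value again 0.127. The sign is lost.

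**3. Expected value with no effect.** For two groups and q response dimensions, multivariate partial eta squared equals 1 − Wilks' lambda. Under the null it follows a Beta(q/2, (N − 1 − q)/2) distribution with mean q/(N − 1). This assumes multivariate normality and no covariates. Simulation with 4,000 runs per setting gave 0.056 for q = 3 and 0.217 for q = 12 at N = 56.

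| Model | q | Null mean, N = 56 | Null mean, N = 84 |
|---|---|---|---|
| One outcome, one contrast | 1 | 1/55 = 0.018 | 1/83 = 0.012 |
| One outcome, three time contrasts | 3 | 3/55 = 0.055 | 3/83 = 0.036 |
| Four primary variables jointly (POMA-T, TUG, estimated BMD, T-score), three contrasts each | 12 | 12/55 = 0.218 | 12/83 = 0.145 |

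The last row applies only if the outcomes are analysed together. It also takes the four variables as linearly independent. If the T-score were an exact linear function of estimated BMD, q would be 9 and the null mean 9/55 = 0.164.

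**4. Like-for-like comparison.** The null value has to be compared with the target effect in the same model. Placing d = 0.75 on one dimension, uncorrelated with the others, with 56 completers gives these mean values:

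- q = 3: about 0.17 with the target effect, against 0.055 with none.
- q = 12: about 0.31 with the target effect, against 0.22 with none.

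The target effect therefore gives the larger value on average in both models. But the same 0.75 SD effect appears as about 0.12, 0.17 or 0.31 depending only on how many dimensions are in the model. That is why the statistic cannot be read back to 1.5 points.

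**The case against.** The strongest case on the other side has four parts.

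*The plan reports other effect measures.* This is right. Falls get a relative risk, which has a direction, and group means and 6-month changes are in each outcome's own units. A reader might infer that partial eta squared is the only effect size in the plan, or that nothing will be reported in points. The article supports neither. A reader could subtract the two mean POMA-T changes and compare the result with 1.5. What is still not named is that difference as the estimate, with an interval.

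*The statistic is not large under the null.* A reader might infer that a programme with no effect would show a substantial partial eta squared. That needs a joint analysis of many outcomes, which section 2.9 never states. The only dimension it spells out is the four time levels, and change is calculated for each outcome. Modelled one outcome at a time, the null mean is 0.018 to 0.055. Setting 0.22 against 0.12, to argue that no effect would look larger than the target, compares a 12-dimensional statistic with a one-dimensional one. Nor should all the outcomes simply be multiplied by three to get a higher figure, because section 2.7.2 defines QUI as an exact linear function of SOS and BUA. The accompanying test also allows for dimension, so a null result would usually be non-significant.

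*Partial eta squared is the customary companion to this model.* That is true, and it is a reason to keep it as a supplement. It does not supply a direction, units or an interval.

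*The reported contrast can be left to the analysis plan, and 1.5 points is a design input, not a success threshold.* Both are fair. The point here is not that detail is missing: the article has chosen the effect metric, and the choice does not fit the design quantity. Reading the estimate against 1.5 points is interpretation and does not add a pass mark.

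**Conclusion.** The point holds in limited form. For the continuous primary outcomes, the efficacy model has one named effect size. It gives 0.127 for a 1.5-point gain and for a 1.5-point loss, carries no units and pools the time points. The other planned summaries soften this but name no between-group difference with a confidence interval.

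The upward bias is secondary. It is about 0.055 on average for one outcome over three contrasts with 56 completers, and up to about 0.22 only under a joint analysis of the four primary variables that the article does not specify. These figures assume normal data, no covariates, 28 completers per group and linearly independent outcomes.

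The sample size of 84 reproduces and is not in question. Nothing here shows that the significance tests are invalid. The weakness lies in how the size of the effect will be reported.

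**What to change.** In section 2.9, make the main effect estimate for each continuous outcome the between-group difference in change from baseline to month 6, adjusted for the baseline value, in that outcome's own units (POMA-T points, TUG seconds, g/cm² for estimated BMD, T-score units), with a 95% confidence interval. Add that the POMA-T estimate and its interval will be read against the 1.5-point difference in section 2.8. Keep partial eta squared, if wanted, as a supplementary figure for each outcome separately.

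The cost is about one sentence. The estimate uses measurements already scheduled and comes from the SPSS package already named. The sample size stays at 84.

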**Methods::**

The study is a 6-month, randomized controlled parallel-group, single-blinded clinical trial. Institutionalized patients with Alzheimer disease will be included. The intervention group will perform a multicomponent physical exercise program in reduced groups, with a frequency of 3 sessions per week, associated with a Mediterranean diet. This program includes strength, balance, and aerobic resistance exercises, and in the main part of the session, also ludic exercises to improve agility, coordination, and balance. The control group will receive usual care. The outcomes to assess are the change of physical functions, such as gait and balance, and the change of bone mineral density by calcaneal quantitative ultrasound, during the study follow-up at 1, 3, and 6 months. This clinical trial will generate more and new evidence on the effects of a multicomponent physical exercise program and Mediterranean diet in patients with Alzheimer disease on risk of falls and osteoporotic fractures, the relation of these with bone mineral density, gait and balance, and the correlations between them.

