### Outcome variables

2.7

In the baseline assessment, all variables will be measured including the sociodemographic variables. Later, all outcome variables will be measured at 1, 3, and 6 months (Fig. 1) and will be codified by the physiotherapist who will conduct the intervention. A summary of outcome variables in summarized in Table 1.

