## Discussion

3

This study is part of a line of research and has been planned in the context of physical exercise as a nonpharmacological treatment, along with other interventions such as diet, in elderly and patients with cognitive impairment, considering them as vulnerable or frail population. There are many studies that are showing the beneficial effects of physical exercise on the changes of aging in elderly^[52,54,57,70]^ and in patients with cognitive decline.^[3,24,30,31,35,36,40,56,58]^ Patients with AD are a growing population group, with disturbing epidemiological data for a near future with important consequences from the health, social, and economic points of view.^[4,5]^

For these reasons, in this study, we want to evaluate the short and medium-term effects of a MPEP associated with a MeDi in people with AD on aspects that can improve their quality of life and their degree of autonomy. Taking into account the frailty of this population and the comorbidities correlated to cognitive decline and aging, we will evaluate a large number of outcome variables to assess the impact of the proposed intervention program on physical functions and bone health status with the intention of reducing the risk of falls and its serious consequences, mainly fractures. In such a way, that this MPEP with a MeDi has several specific objectives that attempt to avoid, delay, and/or minimize some of the frail conditions of these patients.

In our study, we want to contribute to the evidence on the reduction of bone fractures and their consequences. To do this, we plan to reduce the risk of fractures, intervening to decrease bone mass loss and the risk of falls as the main causal factors of fractures in older people and, even more, in people with cognitive impairment, such as patients with AD. There are studies that have addressed these aspects separately, but there are no studies that have worked on them together, and we will also look for associations or correlations between them. For this reason, we also will create a registry of falls to see the preventive effect of the intervention, as well as the relationships of each outcome variable with falls. During the 6 months of the study, changes in BMD, gait and balance, and nutritional status will be monitored and analyzed.

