### Strengths and limitations

3.1

We consider having some strengths points in our study. The design of this study has been based on the experience and results of previous pilot study and preliminary nonrandomized controlled clinical trial. The procedures will be carefully conducted by a multidisciplinary professional group highly qualified in the care and treatment of patients with AD. The novelty of our study is based on the fact that it is the first longitudinal clinical trial aimed at assessing the effects of a MPEP with a MeDi in short- and medium-term over 6 months on the bone health status and the risk of falls by correlating them with gait and balance disorders.

Some limitations of this study should be noted. General conclusions can only be drawn with caution and no conclusions about our intervention results should be drawn beyond institutionalized patients with AD, which suggests that they are more affected. Finding eligible elderly people with AD, who do not attend a center where they receive some type of intervention with physical exercise, is currently difficult, which makes intervention biases easily can appear. This can considerably increase drop-out rate during follow-up and the length of the recruitment period. Other studies should attempt to address strategies to increase the recruitment capacity of eligible patients for the control group, and to carry out experimental designs with 2 or more intervention arms.

In our future studies, in the same line of research, we also want to assess in greater depth the impact of diet combined with exercise on our outcome variables and analyze the influence of the nutritional status of patients with cognitive impairment, as well as their relationships with physical, cognitive, and bone health. And the study results will be released to the participating physicians, referring physicians, patients, and the general medical community.

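### One Pearson correlation serves two questions: taken at a visit it cannot show that outcomes change together, and for change scores the handling of arm is not stated

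*Protocol article*

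**What the plan says.** Section 2.9 (Statistical analysis) names one statistic: "We will carry out correlations with Pearson" r. Its purpose is to find out "whether the values of 2 or more quantitative variables change in conjunction or are related in some of the moment of the study", followed by a bracketed reference to the "time-factor in the statistical model". The section does not say whether r is computed on visit values or on changes from baseline, or whether the two arms are pooled, separated or adjusted for.

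Section 2.7 gives the time points: after baseline, "all outcome variables will be measured at 1, 3, and 6 months". Change scores do appear in section 2.9, but in a separate sentence that is not linked to the correlations: "The main change from baseline to 6 months will be calculated by using intention-to-treat analysis for each outcome measure". The 0.05 significance threshold applies to every analysis, and the correlations are not labelled exploratory.

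The correlations are presented as a product of the trial. The Methods part of the abstract ends its list of expected evidence with "and the correlations between them". The Discussion says "we will also look for associations or correlations between them". Section 3.1 describes the novelty as assessing the programme's effects "on the bone health status and the risk of falls by correlating them with gait and balance disorders".

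**The concern.** Whether two outcomes are related at a visit is a question about differences between patients. Whether they change together is a question about differences within patients over time. A fitter patient may have both better bone and better balance at every visit, while the changes in the two over six months are unrelated. A visit-level r is then clearly non-zero and says nothing about joint change.

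The words 'values' and 'moment of the study' point most naturally to r at each visit, yet the same sentence offers that r as evidence of joint change.

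Reading the sentence as change scores leaves a different gap. If the programme improves both outcomes, the treated arm has larger changes in both and the control arm smaller changes in both. Ignoring arm then produces a correlation even when changes within each arm are independent.

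At stake is a statement the authors are likely to want to make: that bone, gait and balance improve together.

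**Working it through.** **Inputs from section 2.8.** POMA-T difference 1.5 points, SD 2, two-sided alpha 0.05, power 80%, 1:1 allocation, dropout 33%, total 84.

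**The plan's own figure.** n per arm = 2 × [(1.960 + 0.842) × 2 / 1.5]² = 27.9, so 28. After dropout, 28 / 0.67 = 41.8, so 42 per arm and 84 in total. The stated size reproduces and is not in dispute. Completers: 2 × 28 = 56.

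**Assumptions not in the documents.**
- Each outcome has visit SD 1, of which a share s = 0.7 to 0.8 of the variance is stable between patients.
- The stable parts of the two outcomes correlate at ρ = 0.3 to 0.5, with 0 as the reference case.
- Visit-to-visit deviations are independent, so there is no joint individual change.
- In the treatment-effect case both outcomes shift by d = 0.75 SD. For POMA-T this is 1.5 / 2; for the second outcome it is assumed.

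**Reading A: r on visit values, no treatment effect.** Expected r = ρ × s, from 0.3 × 0.7 = 0.21 to 0.5 × 0.8 = 0.40. At n = 56 the critical |r| is 0.263. The chance of P < .05 follows from Fisher's z with standard error 1/√53:
- r = 0.21: atanh(0.21) × √53 = 0.213 × 7.28 = 1.55; P(Z > 1.96 − 1.55) = 34%.
- r = 0.40: 0.424 × 7.28 = 3.08; P(Z > 1.96 − 3.08) = 87%.
- r = 0: 5%.

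Simulation gives 34% and 88% at the two ends. Adjusting the visit-level r for arm leaves it at about 33 to 88%, so the problem does not come from pooling the arms.

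**Reading B: r on change from baseline, arm ignored, both outcomes shifted.** With 1:1 allocation the arm difference adds d²/4 = 0.75²/4 = 0.141 to the covariance of the two changes and to the variance of each. Within-arm variance of a change is 2(1 − s).
- s = 0.7: r = 0.141 / (0.141 + 0.60) = 0.19; about 29% significant at n = 56.
- s = 0.8: r = 0.141 / (0.141 + 0.40) = 0.26; about 49% significant.

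Simulations across the assumed range gave 27 to 53%.

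Section 2.8 does not say whether the SD of 2 belongs to the POMA-T level or to its change. If it belongs to the change, and the second outcome again has the same standardised shift, r = 0.141 / 1.141 = 0.12, and about 15% of trials are significant.

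**Change from baseline, adjusted for arm.** Under the same conditions r averages 0 and is significant in about 4 to 6% of trials, which is the nominal rate.

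**The case against.** The strongest reply is that the sentence is ambiguous rather than wrong. Its two purposes are joined by 'or', and a visit-level r properly serves the second. The first could mean change scores, which section 2.9 computes for every outcome anyway. A significant visit-level r is also no false positive for a relation at that visit; it misleads only if reported as joint change. The correlations support the main analysis, the article is condensed, and an analysis plan may settle the details. All of this stands. It lowers the weight of the point but does not remove it, because the published sentence ties one statistic to both claims and neither reading is sound for joint change as written.

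Some stronger readings are tempting, and the text does not support them:
- **The plan pools the arms.** It is silent on arm.
- **The novelty rests on these correlations.** Section 3.1 also rests it on the programme's effects, which the randomised comparison by repeated-measures MANOVA addresses.
- **Every pair of outcomes will be tested at every visit**, so that false positives can be counted. No set of pairs is given.
- **Parameters linked by formula will be correlated with each other**, such as QUI with BUA and SOS, or **Pearson r will be used for fall counts.** Neither is stated. Falls have their own analysis in section 2.9.

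**Conclusion.** The point holds in a limited form. Section 2.9 uses one Pearson r for two questions. At a visit it answers only whether variables are related at that time. On change scores it would need a rule for arm that the text does not give.

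With 56 completers and no joint change, a visit-level r is significant in about 34 to 88% of trials. An unadjusted change-score r is significant in about 27 to 53% if both outcomes shift by 0.75 of the visit-level SD. These sizes depend on the assumed between-person correlation, stable share of variance and common shift. With zero between-person correlation and no treatment effect, the rate is the nominal 5%. A reader might infer that the trial will report spurious joint change; the supported statement is that it could.

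The primary treatment comparison and the sample size are not affected. The correction is worth making because the abstract, the Discussion and section 3.1 all advertise the correlations.

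**What to change.** Replace the correlation sentence in section 2.9 with one that separates the two questions:
- **Joint change:** correlate change from baseline to month 6, adjusted for arm (partial correlation, or computed within arm). Name in advance the few pairs that serve the aim, for example estimated BMD with POMA-T and estimated BMD with TUG. Report r with its 95% CI and label the result exploratory.
- **Relation at a visit:** keep the single-visit correlations if wanted, and describe them only as cross-sectional.

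The cost is a revised sentence and a few lines of SPSS syntax, with no new data or visits. The downside is fewer significant correlations to report.
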